### Sample size estimation

Sample size estimation in this RCT is based on the expected fat loss following four weeks of hypoxia exposure plus exercise and dieting. The data of our preliminary experiment showed that the means of fat percentage decrease in the normoxia and hypoxia groups were 3.1 and 6.0% respectively, and the standard deviation of the change was about 3%. It is estimated that a sample size of 17 participants per group will be required to observe a similar result with a power of 80%. Considering a 15% dropout and exit rate, we will recruit 40 subjects with 20 in each group.

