### Data management and statistical analysis

Data generated in the study will be collected and summarized using mean (standard deviation) values. Group differences in demographical and clinical characteristics at baseline will be tested using a two-sample t-test for quantitative data and chi-square test for qualitative data. Repeated measures analysis of variance (RM ANOVA) will be used to analyze the main effect of treatment and potential time-by-treatment interactions. For these analyses, parametric assumptions of the normality and homoscedasticity will be checked using standard tests and graphical methods. If those assumptions are violated, data transformation and non-parametric procedures will be considered sequentially. Multivariate regression analysis will be performed to analyze the relationship between changes in body composition, appetite score, and gastrointestinal hormones following intervention and during follow-up. Multiple models will be developed and tested for different sets of outcome measures and regressor variables. All statistical analyses will be performed using the Statistical Package for the Social Sciences (SPSS, Inc., Chicago, Illinois, United States) for Windows version 18.0, and a significance level of 0.05 will be used.

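### Assumption checks may replace the primary analysis, and nothing requires the replacement to keep the between-group difference in change on which the trial was sized

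*Protocol article*

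**What the plan says.** The section Data management and statistical analysis names the model: "Repeated measures analysis of variance (RM ANOVA) will be used to analyze the main effect of treatment and potential time-by-treatment interactions". It adds that "parametric assumptions of the normality and homoscedasticity will be checked using standard tests and graphical methods". The rule that follows is: "If those assumptions are violated, data transformation and non-parametric procedures will be considered sequentially". On the level it says only that "a significance level of 0.05 will be used". The section does not say which checks are meant, at what level, or on what unit (raw values per arm and visit, model residuals, or changes). It names neither the transformation nor the non-parametric procedure.

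The section Sample size estimation rests on change from baseline. From the preliminary experiment, "the means of fat percentage decrease in the normoxia and hypoxia groups were 3.1 and 6.0% respectively". For the spread, the article reports that "the standard deviation of the change was about 3" percent. From these figures the article concludes that "a sample size of 17 participants per group will be required to observe a similar result with a power of 80" percent.

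**The concern.** The trial is sized on how much more fat percentage falls in one arm than in the other. In the planned model that quantity is the time-by-treatment contrast. The fallback rule allows another analysis to take its place once the outcome data have been examined, and does not say that this analysis must address the same contrast. Some familiar non-parametric choices would not. Friedman or Wilcoxon tests within an arm compare visits, not arms. A Mann-Whitney test at one visit compares arms but ignores baseline. A transformation keeps a comparison of arms but moves it off the percentage-point scale used for sizing.

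Two things are at stake: which question the primary result answers, and, if the fallback drops the change, power in a trial with little to spare.

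**Working it through.** **1. The plan's own figure.** Difference 6.0 − 3.1 = 2.9 points; SD of change 3; two-sided 0.05 (sidedness is not stated, so this is an assumption); power 80%.

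Normal formula: n = 2 × (1.960 + 0.842)² × 3² / 2.9² = 16.8, so 17 per group. Allowing for dropout, 17 / 0.85 = 20 per group, 40 in total. Both stated figures reproduce. With the exact t distribution, power is 0.78 at 17 per group and 0.85 at 20. The calculation is a comparison of changes between arms.

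**2. Assumptions for the check.** None of these is in the article.
- 17 per arm, three visits, perfectly normal data with equal variances, SD of change 3, equal correlation ρ between visits.
- ρ = 0.5, 0.7 or 0.9. The single-visit SD is then 3 / √(2(1 − ρ)) = 3.0, 3.9 or 6.7 points.
- Cell-wise checks: six Shapiro-Wilk tests (2 arms × 3 visits) and three Levene tests, each at 0.05, with any rejection counted as a violation.
- On a violation the analysis goes straight to the fallback. The transformation step was not simulated.
- 3,000 simulated trials per setting.

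**3. How often the checks trigger by chance.** Cell-wise, in 28% to 33% of trials. With one pooled residual test plus one Levene test, in about 8%.

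**4. Power at the four-week contrast, true difference 2.9, cell-wise checks.**

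| | ρ = 0.5 | ρ = 0.7 | ρ = 0.9 |
|---|---|---|---|
| t-test on change, always | 0.783 | 0.784 | 0.782 |
| Mann-Whitney on change, always | 0.765 | 0.759 | 0.756 |
| Mann-Whitney on post values, always | 0.751 | 0.544 | 0.226 |
| Chance trigger | 0.331 | 0.327 | 0.278 |
| Two-stage, fallback on change | 0.776 | 0.774 | 0.773 |
| Two-stage, fallback on post values | 0.776 | 0.700 | 0.636 |

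Hand check of the last cell, treating trigger and result as independent: 0.722 × 0.782 + 0.278 × 0.226 = 0.627, close to the simulated 0.636. The loss grows with ρ because the standardised effect on post values is 2.9/3.0 = 0.97, 2.9/3.9 = 0.74 and 2.9/6.7 = 0.43, whereas on change it stays at 2.9/3 = 0.97.

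With the 8% trigger, the loss at ρ = 0.9 is only about 0.08 × (0.782 − 0.226) = 0.04.

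**5. Type I error.** With no true difference, the two-stage procedure rejected in 0.044 to 0.051 of trials under either fallback.

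**6. The fixed contrast.** Adjusting the four-week value for baseline reduces the relevant variance from 9 to 9 × (1 + ρ)/2 = 6.75, 7.65 or 8.55. Simulated power at 17 per arm is then about 0.87, 0.82 and 0.79, equal to or above the t-test on change.

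**The case against.** The strongest reply is that the article describes nothing harmful. It says that alternatives will be considered, puts transformation first, and names no rank test. The rule is attached to the analyses of treatment effect and time-by-treatment interaction, so it can be read as keeping those targets. A permutation test or a rank test on change is non-parametric and preserves the contrast. The trigger rate of about 30% depends on nine separate tests with any rejection decisive, and a pooled check brings it to 8%. A separate analysis plan may settle all of this.

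Much of that stands. A reader might infer that the rule does replace the primary analysis with tests that ignore time-by-treatment; the text permits this but does not say it. A reader might also infer that the 0.05 level is lost; the simulated switch shows no inflation. Choosing among results already seen was not simulated, and the article does not describe it. Nor is the silence on sphericity an error: the article does not say that the three-visit F test will be uncorrected, and such a correction is ordinary analysis-plan detail.

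What the reply does not remove is that the article states a rule instead of leaving the matter open. That rule makes the primary test depend on the outcome data and allows a fallback that drops the sized contrast as readily as one that keeps it.

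**Conclusion.** The point holds as a weakness in a stated rule. The primary analysis can change after assumption checks, to an unnamed method that need not estimate or test the difference in change.

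The size depends on choices the article leaves open. If the fallback works on change scores, the cost is 1 to 2 points of power. If it is a Mann-Whitney test on post-intervention values with cell-wise checks, overall power falls from 0.78 to about 0.70 at a within-child correlation of 0.7 and 0.64 at 0.9, with almost no loss at 0.5. A pooled check limits the loss to about 4 points even at 0.9. These figures rest on assumed correlations, assumed checks, ideal normal data and an unmodelled transformation step. They show what the wording allows and do not predict what the trial will do.

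The change is worth making because it is cheap and because exact power at 17 per group is already just under the 80% target.

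**What to change.** For the primary outcome, replace the sequential fallback with one fixed contrast: the between-group difference in four-week change in total body fat percentage, adjusted for baseline and gender, reported whatever the diagnostics show. Fixing the contrast requires naming one of the listed DXA variables and one time; this choice matches the fat-percentage change over four weeks used for sizing, and gender is already the stratification factor.

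Allow a non-parametric analysis only as one pre-stated sensitivity test of the same contrast, for example a permutation test stratified by gender. Transformation may remain an option for the hormone and IL-6 assays.

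The cost is a few sentences and one extra resampling run, with no additional participants or measurements. What is given up is the freedom to switch the primary test after seeing the data.

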It is accepted that in response to weight loss, counter-regulatory adaptations develop in the appetite regulatory system, including the gastrointestinal hormones, defending impositions that promote a negative energy balance. Different weight loss intervention approaches are likely to cause different counter-regulatory adaptations in terms of the content and the magnitude of the response. There is some evidence suggesting that diet-induced weight loss is associated with a compensatory increase in total ghrelin (GT) plasma levels and a blunted postprandial release of PYY and GLP-1 [7,8]. Exercise-induced weight loss may increase the drive to eat, as shown by increased levels of acylated ghrelin (AG) and subjective feelings of hunger in fasting, but it may also improve satiety as evidenced by an increase in the late postprandial release of GLP-1 after exercise training [9].

Few studies have investigated the combined effect of exercise and dieting on appetite in children and adolescents. Based on the limited data, it appears that ghrelin levels increase after a weight reduction program, with no change in PYY levels [10-13]. Similarly, we have observed an increase in ghrelin concentrations after weight loss in adolescents who participated in an exercise and diet intervention for four weeks in a summer camp program in a previous study (unpublished data).

Recently, the effect of high altitude on appetite regulation has attracted researchers’ interest. It is a widely observed phenomenon that a high altitude can induce loss of appetite [14-16]. In many studies, loss of appetite and the resulting decrease in energy intake have been attributed to acute mountain sickness (AMS), symptoms of which include headache and anorexia. However, loss of appetite cannot merely be a by-product of AMS because anorexia and weight loss still persist when symptoms of AMS have subsided [17]. Furthermore, studies conducted in normobaric hypoxia chambers, where other environmental stressors associated with high altitude are eliminated (extreme cold and physical exertion), have demonstrated that hypoxia *per se* can cause reduced appetite and energy intake, and loss of body weight [18]. It has been suggested that the effect of hypoxia on appetite is mediated by the changes in gastrointestinal hormones [19-22].

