It is perceivable that to promote success in longterm weight loss, hypoxia can be implemented in a traditional diet and exercise weight loss program, because the negative effect of hypoxia on appetite might be able to balance the positive effect of diet and exercise. Exercise and hypoxia have been used in combination in sports to induce maximal increase in aerobic endurance in athletes, but have rarely been used in weight loss, especially in children and adolescents. We have run several sessions of weight loss summer camps designed for obese adolescents in Shanghai, China. The effect of exercise and hypoxia on weight loss has been explored in our preliminary studies and interesting results have been generated [23,24]. As such, we are now designing a randomly controlled trial to systematically investigate the longterm weight loss effect of exercise with hypoxia in obese adolescents and determine the mediating effect of the gastrointestinal hormones. We hypothesize that: 1) exercise and hypoxia will have an additive effect on weight loss via increasing energy expenditure and suppressing appetite; 2) hypoxia use will lead to less rebound of weight loss after intervention due to its potential negating effects on compensatory changes in appetite elicited by exercise and diet in a traditional weight loss program; and 3) changes in gastrointestinal hormones (including ghrelin, PYY, CCK, and GLP-1), as well as in cytokine interleukin (IL)-6, will be associated with changes in body weight after the intervention and during follow-up.

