### Aims

The aims of this randomized controlled trial (RCT) are to evaluate the effectiveness of intermittent hypoxia and exercise, in combination with a balanced diet, on inducing short- and longterm fat loss in Chinese children and adolescents, and to determine the molecular mechanisms behind the benefits of hypoxia in enhancing weight loss.

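### The protocol promises to determine hormonal mediation, but its only hormone-to-fat analysis is an open set of change-on-change regressions at 0.05, which can show association but not mediation

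*Protocol article*

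**What the plan says.** The protocol article describes the mechanistic goal in two strengths.

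- **Strong.** The end of the Background says the trial will "determine the mediating effect of the gastrointestinal hormones". The Aims add a purpose "to determine the molecular mechanisms behind the benefits of hypoxia in enhancing weight loss".
- **Weaker.** Hypothesis 3, in the same Background paragraph, expects only that changes in ghrelin, PYY, CCK, GLP-1 and IL-6 go together with changes in body weight, after the intervention and over follow-up. The Abstract speaks of exploring a potential mechanism, and the Discussion says IL-6 might play a part.

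The section on data management and statistical analysis gives one analysis that connects markers to body composition. It is a regression "to analyze the relationship between changes in body composition, appetite score, and gastrointestinal hormones following intervention" and during follow-up. The next sentence reads "Multiple models will be developed and tested for different sets of outcome measures and regressor variables". For all analyses, "a significance level of 0.05 will be used". Treatment is named only for the repeated measures ANOVA.

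On direction of effect, the Background reports evidence that "diet-induced weight loss is associated with a compensatory increase in total ghrelin (GT) plasma levels", and that the team itself saw ghrelin rise after weight loss in an earlier camp.

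**The concern.** A mediation claim needs three things: hypoxia moves the hormone, the hormone moves fat at a given arm, and the effect runs in that direction. A regression of fat change on hormone change gives an association between the two and estimates no indirect effect. Leaving the set of models open at an unadjusted 0.05 adds a second problem, because some links will probably appear by chance.

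At stake is the trial's second aim. An association produced by reverse causation, by a search over many models or, if arm is omitted, by arm assignment could be published as the mechanism by which hypoxia aids weight loss.

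**Working it through.** **1. The plan's own figure.** Inputs from the sample size section: "the means of fat percentage decrease in the normoxia and hypoxia groups were 3.1 and 6.0% respectively", SD of change about 3, power 80%, dropout 15%. The 0.05 level comes from the statistical section; two-sided is assumed.

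n = 2 × (1.960 + 0.842)² × 3² / 2.9² = 2 × 7.85 × 9 / 8.41 = 16.8, so 17 per group. Then 17 / 0.85 = 20 per group. Both stated figures reproduce. For the steps below this gives 34 completers (40 recruited) and an arm effect on fat of 2.9 / 3 = 0.967 SD.

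**2. What each planned analysis can show.**

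- Repeated measures ANOVA: whether hypoxia shifts a hormone, and whether it shifts fat. It does not connect the two.
- Change-on-change regression: whether hormone change and fat change go together. If fat loss raises ghrelin, as the Background reports for diet-induced loss, the slope is non-zero even when ghrelin mediates nothing.
- Hormones and fat are measured at the same three visits, so changes over the same interval cannot be ordered in time.

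**3. Size of the possible search.** The markers are leptin, ghrelin, PYY, CCK, GLP-1 and IL-6 (6), or 7 with the appetite score. There are five DXA measures and two intervals. So 6 × 5 × 2 = 60 pairs, or 7 × 5 × 2 = 70. With m tests and every null true, the expected number of false links is 0.05m. If the tests are independent, the chance of at least one is 1 − 0.95^m.

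| Tests m | Expected false links | Chance of at least one |
|---|---|---|
| 6 (one outcome, one interval) | 0.3 | 26.5% |
| 30 | 1.5 | 78.5% |
| 60 | 3.0 | 95.4% |
| 70 | 3.5 | 97.2% |

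With correlated measures (assumed r of 0.5 to 0.95 among outcomes and 0 to 0.6 among markers, N=34, simulated), the chance is 51% to 92% for 60 tests and 19% to 27% for 6. The expected count for 60 tests stays at about 3.

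**4. What depends on arm.** Suppose hypoxia shifts fat by 0.967 SD and a hormone by d SD, with no link between them within arms. With arms pooled and equal in size, the correlation is

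r = (d × 0.967 / 4) / √[(1 + d²/4)(1 + 0.967²/4)].

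For d = 1.0 this is 0.242 / √(1.25 × 1.234) = 0.195. Share of 20,000 simulated trials with p < 0.05 for the hormone:

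| d (assumed) | r | Arm omitted, N=34 | Arm included, N=34 | Arm omitted, N=40 |
|---|---|---|---|---|
| 0.5 | 0.106 | 8.9% | 5.0% | 9.7% |
| 1.0 | 0.195 | 20.1% | 5.1% | 23.3% |
| 1.5 | 0.261 | 33.7% | 5.0% | 38.7% |

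Including arm removes this source of error. It does not remove reverse causation, which acts within arms.

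**5. Would a lagged model be enough?** One could regress two-month %TBF on week-4 hormone change, adjusting for week-4 %TBF. With N=34, a 1 SD hormone shift and week-4 fat loss fully mediated by the hormone (all but N assumed), the hormone term was significant in only about 5% of simulated trials, the nominal error rate. Conditioning on week-4 %TBF removes the effect already carried during the intervention, so this model can speak to rebound only.

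**The case against.** Several points on the other side are sound.

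- **The treatment term.** A reader might infer that the protocol pools the arms without adjusting for treatment. It does not say so. It lists no regressors, arm may be among them, and a covariate list is something a condensed article may leave to the full plan. The 9% to 34% is therefore a conditional risk, not a stated defect.
- **Hypothesis 3.** A reader might infer that hypothesis 3 itself is tested wrongly. It asks only for association, and an association regression is its matching analysis. If hypoxia moves both hormone and fat, the pooled association is real; it misleads only when read as mediation.
- **Number of tests.** The 60 to 70 pairs are a count of what is possible. The text speaks of multivariate regression and fixes no number, and about 3 false links requires every null to be true. That false links are certain does not follow; that a wide search is likely to give some does.
- **Data-driven selection.** The text does not say that models will be chosen on the trial data, nor does it rule out a lagged model.
- **Softer wording.** The Abstract and Discussion already use exploratory language, and the repeated measures ANOVA covers the treatment-to-hormone step.

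What remains rests on stated text. The Background and Aims promise to determine mediation and mechanisms, and the one analysis offered for the hormone-to-fat step is an open set of associational models.

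**Conclusion.** The concern holds as a mismatch between claim and analysis. The planned regressions can support hypothesis 3 but cannot establish mediation, because the protocol itself reports that weight loss shifts these hormones and because no indirect effect is planned. The open model set at 0.05 makes some false links likely. The chance of at least one runs from roughly 19% to 27% for six tests to 51% to 95% for sixty, across the correlated and independent cases and with all nulls true.

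The error from omitting arm applies only if arm is in fact omitted and hypoxia does shift the hormone. The shifts and correlations used here are assumptions, since the document gives none. The analyses are secondary: the primary body composition comparison and the sample size stand as they are. The change should be made, but the trial's main result does not depend on it.

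**What to change.** 1. In the statistical section, pre-name one model form: week-4 %TBF on arm, week-4 hormone change, baseline %TBF and sex. Fit it for each of the five hypothesis 3 markers (ghrelin, PYY, CCK, GLP-1, IL-6). Report the indirect effect (arm effect on the hormone times hormone coefficient given arm) with a bootstrap confidence interval, and apply Holm adjustment over the five.
2. Add the lagged two-month model, which also adjusts for week-4 %TBF, only as a separate analysis of rebound. It should not be the sole mediation model, for the reason in step 5 of the working.
3. Label all other models exploratory.
4. In the Background and Aims, replace the promise to determine the mediating effect and the molecular mechanisms with exploring associations consistent with mediation. This is still needed with the model in item 1, because hormone and fat changes over the same four weeks cannot be ordered in time.

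The cost is a change of analysis text and aims wording, with no new data or visits. The downside is a weaker mechanistic claim.

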## Discussion

To the best of our knowledge, our study will be the first to evaluate the effectiveness of ‘sleep high and train low’ on short- and longterm weight loss among obese adolescents. The study will focus on obese adolescents due to the rising prevalence of obese children in China and the adverse impact of childhood obesity on adult health. Adolescent obesity has been attributed mainly to a sedentary lifestyle and an unhealthy diet. In China, a great effort has been made to use exercise and dietary intervention to treat obesity and metabolic disorders in children. However, the weight rebound following most of the weight loss programs has made such an effort fruitless. The weight rebound is believed to be caused by the compensatory increase in appetite induced by exercise and diet. Conceivably, the agent that can counteract this compensatory effect will benefit obese patients in achieving longterm weight loss. Hypoxia is potentially one of such agents: the anorexia effect of hypoxia has been widely observed and might be utilized to dampen the appetite compensatory effect of exercise and diet, thereby promoting the success of weight loss in the longterm. Due to the profound benefits of exercise training and diet in the obese population, we do not expect to use hypoxia as a replacement, but rather as a supplement to exercise and diet intervention. Therefore, children in the control group will undergo the same exercise training and diet as the hypoxic group in order to evaluate the value of hypoxia in promoting weight loss, and minimizing weight rebound after intervention.

Instead of using continuous hypoxic exposure such as high altitude, we choose to use intermittent hypoxic exposure, which has been recommended as an option for the free-living obese population [30]. The effect of intermittent hypoxia exposure on weight reduction has been reported previously. In a model of diet-induced obese mice, it has been shown that intermittent hypoxic exposure induced decreases in body mass, blood glucose levels, and cholesterol erythropoietin concentrations [27,31]. In a few human studies, the synergistic effect of exercise and hypoxia in treating obesity and associated metabolic disorders has been demonstrated, where low intensity exercise training at normobaric hypoxic condition (15% O_2_) led to more weight loss and greater improvement in metabolic health compared to training at ambient conditions (21% O_2_) [32-34]. However, further evidence-based studies are needed to carefully evaluate the therapeutic value of hypoxia and the model of utilization in treating obesity, especially in children. Intermittent hypoxia exposure, as used in the ‘sleep high and train low’ paradigm has been proposed for endurance athletes to maximally enhance their endurance exercise capabilities, however the clinical use of intermittent hypoxia in the management of cardiometabolic diseases has rarely been tested. Our study will be the first to evaluate the effect of ‘sleep high and train low’ on weight loss in obese adolescents. Through monitoring a wide spectrum of health indices including blood pressure, heart rate, vital capacity, blood glucose and insulin levels, blood lipid profile, and immune function we will careful monitor any possible side effects associated with hypoxia exposure.

Furthermore, we will investigate the mechanism for the effect of hypoxia on weight management. We will focus on the regulatory effect of ‘sleep high and train low’ on gastrointestinal hormones levels. In addition, we hypothesize that the cytokine IL-6 might also play a role in mediating the appetite regulatory effect of exercise (positive effect) and hypoxia (negative effect). The clarification of mechanisms leading to weight loss in ‘sleep high and train low’ might provide information for the development of new strategies in combating obesity in the future.

